In this study, the results of blood tests performed as part of the standard management protocol used at the study clinic will be analyzed. Thus, no additional blood tests will be performed due to the study, and results from the blood tests performed routinely on the patients per their treatment protocol will be collected and analyzed for the purpose of this study.

Collection of human-derived materials (blood): 35 ㎕ of blood will be collected through a finger puncture and immediately placed in the kit for analysis using a LABGEO PT10 Analyzer.

Analysis of human-derived materials (blood): blood sample will be analyzed using a LABGEO PT10 Analyzer

Disposal of human-derived materials (blood): After analysis, the blood will be placed in a biohazard waste container and will be discarded with other biohazard wastes twice a month by a biohazard waste removal company (Munhwa Green, [name]).

1. Observation parameters
2. Sociodemographic information
3. History taking
4. History
5. Surgical history
6. Medication history

* Information about antihypertensive medication use will be collected.
* If the patient is taking antihypertensive drugs, they are instructed to notify the investigator regarding the dosage of the drug and any changes to the dosage.
* Patients are informed to maintain their normal lifestyle, including exercise and diet.

1. Measurement items
2. Height and VS (excluding BP and pulse): 5 minutes of measurement followed by 15-min rest
3. BP and pulse
   - - 1. Measurement device: electronic blood pressure cuff Omron Healthcare (Model: HEM-9000AI)
       2. Measurement items

- MSSBP (Unit: mmHg)
- MSDBP (Unit: mmHg)
- Pulse (Unit: beats/min)
  - - 1. Measurement method
- **Definition of MSBP:** the average of **three or more measurements** taken with at least 2 minutes apart is used. BP is measured in a straight seated position (seated BP).
- **Arm selection**: BP is measured from both arms if possible, and the arm with the higher BP is selected. Subsequent BP measurements must be taken from the same arm.
- Posture should remain unchanged while measuring BP. A supine or seated position must be maintained for at least five minutes, and a standing posture must be maintained for at least one minute before taking the measurements.

1. Blood test
   - - 1. Measurement device: LABGEO PT10 Analyzer

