       2. Measurement items: Aspatate transaminase(AST), Alanine transaminase(ALT), Gamma glutamyl peptidase(GGT), Total Bilirubin, BUN, Creatinine, Total cholesterol, Glucose
       3. Measurement method

- Refrain from caffeine, alcohol, and tobacco consumption the day before the test
- 8-hour fasting is required before the test; water allowed
- Test takes 10 minutes

1. [**3D Blood pressure and pulse wave test]**: **3d pulse wave imaging device (3D MAC, ㈜ Daeyomedi Co., Ltd., South Korea)**: 10 minutes ( See [Attachment 1])
   - - 1. Pulse strength value and stage (Unit:gf)
       2. Pulse depth value and stage (Unit:gf/cm^2)
       3. Pulse velocity value and stage (Unit:beats)
       4. Pulse shape value and stage (Unit:step)
       5. Radial artery augmentation index(R-AI) (Unit:%)
       6. SBP (Unit:mmHg)
       7. DBP (Unit:mmHg)
       8. Pulse pressure (PP) (Unit:mmHg)
       9. Pulse rate (PR) (Unit:beats/min)
       10. Cardiac output (1 beat) SV (Unit:mL/beat)
       11. Cardiac output (1 minute) CO (Unit:L/min)
       12. Systemic vascular resistance index(SVRI) (Unit:dyn*s/cm^5/m^2)
2. European Quality of Life Five Dimension Five Level Scale (EQ-5D-5L) questionnaire: 5 minutes ( see [Attachment2] )
3. Other

Adverse events and concomitant treatments are monitored per patient’s report and questions at every visit

1. Outcome measurement criteria and method
2. Primary outcome

This study is an exploratory observational study aiming to explore the safety and BP-lowering effetcs of modified SMS prepared and prescribed by Kyung Hee Bi, Che, Dam Korean Medicine Clinic for patients with HTN by comparing SBP before and after treatment.

1. [Changes in MSSBP] use Omron Healthcare HEM-9000AI
   Amount of change in MSSBP at end of treatment (visit 3) compared to the baseline (visit 1)
   - - 1. Null hypothesis (H0): There is no difference in MSSBP between the baseline (Visit 1) and end of treatment (visit 3).
       2. Alternative hypothesis (HA): There is a difference in MSSBP between the baseline (Visit 1) and end of treatment (visit 3).
2. Secondary outcome
3. Amount of change of MSSBP at visit 2 compared to the baseline (visit 1)
4. Amount of change of MSSBP at visits 2 and 3 compared to the baseline (visit 1)
5. Percentage of participants with normalized BP: percentage of patients who achieved normal BP compared to MSSBP/MSDBP measured at each time point (percentage of patients who had a BP of less than 140/90 mmHg at end of treatment)

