1. Adverse events anticipated from use of modified SMS during routine treatment process

There is a low risk for AEs anticipated due to the use of modified SMS (risk for adverse effects and tolerance to modified SMS), but there is a risk for the following AEs that may occur with the routine treatment protocol:

- Gastrointestinal symptoms (Indigestion, heartburn)
- Autonomic nervous system symptoms (palpitation)

Thus, other than the AEs associated with the use of modified SMS for therapeutic purposes, there is little to no anticipated risks or adverse effects from study participation.

1. Usage precautions

- The participants are educated about the following precautions when taking the herbal medicine:
- Keep the herbal medicine in a cool place or in the refrigerator.
- Once opened, take the herbal medicine as soon as possible, and any opened herbal medicine must be kept in the refrigerator within two days.

1. Education on AEs

The PI and co-investigators of the observational study will inform the participants or their caregivers about the potential AEs following the use of modified SMS during the study period and explain that there is little risk for additional AEs from study participation because the study does not involve additional intervention or tests other than those included in the routine treatment protocol. The participants should also be informed to contact the research team immediately upon developing an AE.

1. Collection and reporting of AEs

At every visit to the Kyung Hee Bi, Che, Dam Korean Medicine Clinic, VS measurements, examination, and questionnaire for the observation parameters, or monitoring of AEs will be performed. If the investigator finds that the participant has clinically significant symptoms or changes and if the study participant voluntarily reports such an event, the investigator will document the incidence, evaluation, and measures for AEs in the CRF using standardized medical terminology.

In case of a serious adverse event (SAE) during study participation, the SAE will be promptly reported via the e-IRB system in accordance with Article 4–25 of the Standard Operating Procedures of the joint IRB. SAE is defined per the Standard Operating Procedures of the joint IRB.

1. Treatment of AEs

If a participant incurs a direct injury from the use of modified SMS as part of the routine treatment process, appropriate medical treatment will be given based on the routine treatment process.

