This study is an observational study collecting clinical data and observing the clinical course of patients taking modified SMS, and there are no interventions other than the herbal medicine regimen or any additional tests required for study participation. If an AE occurs nonetheless, the herbal medicine regimen will be discontinued, and the patient will be observed and treated as necessary until the event is resolved per the general treatment protocol at Kyung Hee Bi, Che, Dam Korean Medicine Clinic.

Measures taken for abnormal blood test results: liver function test including aspartate transaminase (AST), Alanine transaminase (ALT), Gamma glutamyl peptidase (GGT), and total bilirubin, as well as BUN, creatinine, total cholesterol, and glucose are measured on visits 1, 2, and 3. Per the general treatment protocol at Kyung Hee Bi, Che, Dam Korean Medicine Clinic, additional use of herbal medicine regimen is suspended if the levels rise more than twofold, along with the standard medical measures (including tests) for f/u.

Given the minimal anticipated side effects, the study is not expected to have substantial safety issues. As a rule, safety parameters are monitored, and any incidence of AEs will be notified to the PI and co-investigators. Upon onset of an AE, appropriate medical measures will be taken until recovery.

1. Evaluation of safety parameters

Safety evaluation will be performed for all AEs that occur during the study period. The rate of AE, rate of AE that led to discontinuation, and rate of SAE are reported. For the rate of AEs, all AEs and AEs associated with Korean medical care and intervention will be presented.

VS or blood test results will be reviewed comprehensively to determine normal/abnormal results, and items deemed clinically significant by the clinician can be analyzed statistically as necessary.

1. Data analysis and statistical methods

Efficacy evaluation will be performed using the FAS. Safety data will be analyzed with the safety set. All analyses will be conducted using the SAS Version 9.4 (SAS Inc, Cary, NC) software, and all statistical tests not defined separately will be performed as a two-tailed test and 5% significance level. Any missing values in the FAS will be imputed using the Last Observation Carried Forward (LOCF) method for the efficacy evaluation. All other data will be analyzed as is.

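### The rule for entering an adverse event in the CRF is worded too narrowly for the all-AE rate the protocol promises, and reading it as two separate triggers does not fully cure this

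*Protocol*

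**What the plan says.** The rule for CRF entry is in Section 14 of the protocol, Collection and reporting of AEs. Its condition is "If the investigator finds that the participant has clinically significant symptoms or changes and if the study participant voluntarily reports such an event". Its consequence is that "the investigator will document the incidence, evaluation, and measures for AEs in the CRF using standardized medical terminology".

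Other places describe a wider scheme:

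- Section 12, Other: "Adverse events and concomitant treatments are monitored per patient’s report and questions at every visit". Table 2 schedules AE monitoring at visits 2, 3 and 4.
- Section 14, Evaluation of safety parameters: "Safety evaluation will be performed for all AEs that occur during the study period". The same paragraph promises the rate of all AEs, of AEs related to the care and intervention, of AEs leading to discontinuation, and of SAEs.
- The same subsection, on test results: "VS or blood test results will be reviewed comprehensively to determine normal/abnormal results", after which "items deemed clinically significant by the clinician can be analyzed statistically as necessary".
- Method, Management of human-derived materials: "results from the blood tests performed routinely on the patients per their treatment protocol will be collected and analyzed for the purpose of this study".
- Section 17, Study termination criteria: one ground for early termination is that more than 25% of the study population have a moderate or severe AE judged related.

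**The concern.** The two conditions are joined by *and if*, and the participant's report is of *such* an event, which ties it back to the investigator's finding. A site that follows the sentence as written would need both. It would also apply clinical significance as a gate before entry rather than as a grade given afterwards.

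Safety is a stated purpose of the study, and there is no control arm against which an under-recorded rate would show up. The AEs the protocol anticipates are indigestion, heartburn and palpitation. These are subjective, often mild, and likely to emerge on questioning. The scheduled blood tests, for their part, can detect changes the participant does not feel. A narrow entry rule works against both kinds of event, and a symptom not written down at the visit may not be recoverable later.

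**Working it through.** No sample-size, power or alpha figure is involved and the plan gives no number to reproduce. The check is to take each kind of event and ask whether it enters the CRF as an AE under each reading of the Section 14 sentence.

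| Event | Both conditions required | Two separate triggers |
|---|---|---|
| Symptom volunteered and judged clinically significant | entered | entered |
| Symptom volunteered, not judged significant | not required | entered, unless *such* an event carries the significance test over |
| Symptom elicited by questioning, judged significant | not required (not volunteered) | entered |
| Symptom elicited by questioning, not judged significant | not required | **not required** |
| Test change without symptoms, judged significant | not required (nobody reports it) | entered |
| Test change without symptoms, not judged significant | not required | not required |

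The first four rows are all within the monitoring described in Section 12, which covers both reports and questions. They are also within the Section 14 evaluation, which is of all AEs without a significance threshold. The literal reading omits three of the four. The two-trigger reading omits the fourth, and possibly the second. Whether the last row is an AE at all depends on a definition that is not in the text available, so the finding does not rest on it.

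**What depends on the entry.**

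- *AE rates.* They are counts of participants with entered events over a denominator. With all 30 planned participants in the Safety Set, each participant whose only AE is not entered lowers the rate by 1/30 = 3.3 percentage points. If only the 20 whom the sample-size section expects to provide data were in the Safety Set, it would be 1/20 = 5.0 points. How many such participants there would be is not derivable.
- *Rate of AEs leading to discontinuation.* Section 14 suspends the product on a more than twofold laboratory rise, with no participant report needed. Under the literal reading, such a suspension in a participant without symptoms need not have an AE behind it in the CRF.
- *Termination criterion.* 0.25 × 30 = 7.5, so the criterion is met at 8 or more of 30 participants. It counts moderate or severe related events only, so unrecorded mild symptoms do not affect it. The exposure comes mainly from the literal reading, under which a moderate event that was found or elicited but not volunteered could be left out.

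**Laboratory analysis.** The Method section says blood results are collected and analysed. The Section 14 sentence then leaves statistical analysis of vital signs and blood results to items the clinician considers significant, as necessary. It does not exclude the other items, but it commits to no summary of them, and the choice is made after results are known by an unblinded clinic that prescribes the product.

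**The case against.** The strongest reply is that this is awkward drafting, probably from translation, and that the sentence means *if A, and also if B*. The rest of the protocol fits that reading better: patients are questioned at every visit, told to contact the team at once about an AE, any AE is notified to the investigators, and all AEs are evaluated. That stands, and the double condition should not be stated as certain. It does not dispose of the point, because the fourth row of the table fails under that reading too.

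A second reply is that the contents list names a Section 15 with a definition of AEs, whose body is not in the text available. No conclusion can be drawn from that. If that section holds a wider entry rule, the Section 14 sentence must be reconciled with it.

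Several stronger readings are tempting, but the documents do not support them:

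- *Silent laboratory changes go unrecorded.* A reader might infer this, but the values are collected, reviewed as normal or abnormal, and acted on without any report from the participant. At most they are not entered as AEs.
- *Events learned of at the visit 4 telephone call cannot qualify.* The sentence says the investigator finds the symptom. It does not demand objective confirmation, and a symptom elicited by telephone can count as found.
- *Only clinician-selected analytes will be analysed.* The sentence is permissive and does not say *only*. Tabulation by visit may also be set out in a statistical analysis plan that is not shown.

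**Conclusion.** The point holds as a defect of wording with consequences for the safety results. The entry rule is ambiguous, too narrow if read literally, and incomplete even on the kinder reading. It is inconsistent with the Section 12 monitoring and with the Section 14 evaluation of all AEs. The direction of any error is downward, for the AE rates and, mainly under the literal reading, for the count behind the 25% criterion.

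The size cannot be stated. It depends on how the site reads the sentence and on how many events are elicited rather than volunteered, or are judged not significant, and the documents give neither. The figures of 3.3 to 5.0 percentage points per missed participant show only how sensitive a rate is with a denominator of 30 down to 20. They do not estimate the undercount.

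The conclusion assumes that no other part of the protocol overrides the Section 14 sentence. The laboratory summary is a secondary matter.

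**What to change.** **Main change (Section 14, Collection and reporting of AEs).** State that an AE is recorded in the CRF when it is found by the investigator, *or* reported spontaneously by the participant, *or* elicited by questioning, *or* shown by a test result. Add that clinical significance, severity and causality are graded after entry and are not conditions of entry. Check the wording against any AE definition in Section 15.

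**Secondary change (Section 14, Evaluation of safety parameters).** Commit to summarising all eight blood analytes and the vital signs by visit (visits 1, 2 and 3) for the whole Safety Set. The summary then does not depend on items picked after results are seen. Further analysis of particular items can remain at the clinician's discretion.

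**Cost.** A sentence or two in each place, slightly more CRF entry and a few more tables. No new test, visit or measurement is needed, since the questions are already asked and the blood results already collected. The reported AE rate may turn out less favourable.

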4. Liver disease or kidney disease requiring treatment
5. Secondary hypertension
6. History of severe CVD: e.g., myocardial infarction, angina, severe arrhythmia
7. Diagnosis of psychiatric disorder or treatment for psychiatric disorder, including depression, within 2 months of visit
8. Other reasons that contraindicate use of modified SMS as determined by the clinician

- (*Reference arm is selected based on the process outlined in “12. Observation parameters-B.Measurement items”)
- (*Mean seated BP is defined in “12. Observation parameters-B.Measurement items”)

1. Control group

A prospective single-group preliminary observational design; there is no control group, and blinding and randomization are not applicable.

1. Anticipated sample size and grounds for sample size determination

This is an exploratory preliminary prospective observational study. In general, preliminary studies require a minimum of 12 participants [9]. In the present study, we aim to obtain data from 30 participants.

F/u is performed every 4 weeks. In general, 67% of participants re-visit the facility on week 4.

To obtain data from 20 participants with a potential 33% dropout rate, **30 participants** are required.

Every month, about 10 patients take modified SMS, so recruiting the target sample size within the study period is feasible.

In preliminary studies, a minimum of 12 participants are generally required. **Given that this study is a preliminary study collecting exploratory data for subsequent studies, as opposed to a study investigating the therapeutic efficacy, recruitment of 30 participants in consideration of potential dropouts is deemed adequate.**

1. Participant recruitment

Participants will be recruited among patients who visit the Kyung Hee Bi, Che, Dam Korean Medicine Clinic and based on the clinician’s assessment and patient consent.

To ensure consistency of recruitment and fairness for potential participants, a recruitment announcement containing the overall information about the study, including its purpose, inclusion and exclusion criteria, and study schedule, will be posted on the bulletin board within the clinic for a specified period. Visitors to the healthcare facility interested in participating in the study can contact via the contact details listed in the announcement or by directly contacting the research team (PI and co-investigators).

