Full Analysis Set(FAS): Per the Intention-to-Treat (ITT) principle, FAS includes participants who have received the herbal medicine preparation at least once and have had at least one measurement of the primary outcome measure

Safety Set (SS): Includes participants who have received the herbal medicine preparation at least once and have had at least one safety-related f/u

For demographic and baseline data, categorical data will be presented as n (%), and continuous data will be presented as mean±SD.

For efficacy parameters, continuous variables will be analyzed with paired t-test or Wilcoxon signed rank test, and categorical variables will be analyzed using the McNemar test or McNemar Exact test depending on their normality.

For safety parameters, adverse drug reactions (ADRs), SAEs, and serious ADRs will be presented as n (%), and differences across time points will be analyzed using the McNemar test or McNemar Exact test.

ANCOVA model will be used for analysis with sociodemographic factors that may affect HTN, such as sex, age, and use of antihypertensive drugs, included as covariates.

1. Withdrawal of consent and discontinuation
2. Discontinuation criteria

Participants may be discontinued from the trial in the following instances:

- Participants or their legal representatives requests discontinuation or participant withdraws consent due to unsatisfactory treatment effects during the study period
- Violation of inclusion criteria or meeting exclusion criteria
- Failure to take the modified SMS even once during the observational study period, despite giving consent and meeting eligibility criteria
- Occurrence of SAE related to the herbal medicine or AE making continuation in the study difficult
- Change of prescription during study
- Participant’s violation of study plan
- Lost to f/u during study period
- Other reasons due to which continuation of study is deemed inappropriate by the investigator

1. Study termination criteria

Upon occurrence of SAE suspected to be caused by the investigational drug, the PI notifies the joint IRB within 24 hours and terminate the study.

The clinical trial may be terminated prematurely in the following cases:

- Harmfulness of investigational product is discovered
- Moderate or severe AE deemed to have a relationship with the clinical trial occurred in more than 25% of the entire study population
- Study poses threat to the safety and well-being of study participants

1. Withdrawal of consent

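### As written, the FAS and LOCF rules can set the primary change to exactly zero for participants seen only at baseline (up to about 10 of 30), while the withdrawal section would remove the same people

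*Protocol*

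**What the plan says.** Four parts of the protocol bear on this.

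- **Data analysis and statistical methods.** Efficacy is analysed in the FAS, and "Any missing values in the FAS will be imputed using the Last Observation Carried Forward (LOCF) method for the efficacy evaluation". The FAS, said to follow the intention-to-treat principle, takes participants who were dosed at least once and "have had at least one measurement of the primary outcome measure". The word post-baseline does not appear. The Safety Set, defined next to it, does require a follow-up. For efficacy, "continuous variables will be analyzed with paired t-test or Wilcoxon signed rank test", with normality given as the basis for choosing and no normality test named.
- **Primary outcome.** The change in MSSBP from visit 1 to visit 3. MSSBP at visit 1 is also an eligibility criterion, so every enrolled participant has one.
- **Anticipated sample size.** "In general, 67% of participants re-visit the facility on week 4". The target of 30 is derived as follows: "To obtain data from 20 participants with a potential 33% dropout rate".
- **Withdrawal of consent and discontinuation.** Loss to follow-up is listed as a discontinuation criterion. The data of anyone who withdraws consent or meets such a criterion are to be left out of the analysis and destroyed.

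**The concern.** Week 4 is the first visit after baseline. A participant who takes the medicine and does not come back then has one MSSBP reading, the baseline. Under the literal FAS wording that reading is enough for inclusion. LOCF then has nothing to carry but the baseline, and visit 3 minus visit 1 equals zero by construction. Participants lost between weeks 4 and 8 would have their week 4 value used for week 8; that is a milder problem and is not counted below.

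Three things follow if these rules are applied. The reported change is a mixture of observed changes and inserted zeros. The inserted values count as observations in the standard error. A block of identical zeros also tends to fail a normality check, which moves the analysis from the paired t-test to the signed-rank test; in its usual form that test drops zero differences. A mean on 30 people could then stand beside a p-value on about 20.

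The study describes itself as preliminary, meant to supply data for later work and to explore the feasibility of a randomised trial. The size and spread of the MSSBP change are therefore its main product.

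**Working it through.** **Inputs from the protocol.** Planned N = 30; 67% return at week 4; 33% dropout; data wanted from 20; two-sided 5% level.

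**Assumptions.** The protocol gives neither an expected change nor an SD. Worked case: observed changes with mean -9 and SD 12 mmHg. Range: means of -5 to -15 and SDs of 10 to 15 mmHg, observed changes taken as normal.

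**1. The plan's own figure.** 20 / (1 - 0.33) = 29.85, rounded up to 30. Reproduced.

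**2. Baseline-only participants.** 30 × 0.33 = 9.9, about 10. The FAS under LOCF then holds 20 observed changes and 10 zeros.

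**3. Mean.** (20 × μ + 10 × 0) / 30 = 0.67 μ. So -9 becomes -6.0, -5 becomes -3.3 and -15 becomes -10.0 mmHg. With better retention the shrinkage is smaller: with 5 baseline-only participants the factor would be 25/30 = 0.83.

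**4. Spread and precision in the worked case.**
- Expected variance with zeros: [19 × 144 + (200/30) × (81 + 144/20)] / 29 = 114.6, so SD 10.7.
- SE with zeros: 10.7 / √30 = 1.95. SE from the 20 observed changes: 12 / √20 = 2.68.
- 95% half-width with zeros: 2.045 × 1.95 = 4.0. Observed only: 2.093 × 2.68 = 5.6 by formula, or 5.5 as an average over simulated samples, because the sample SD averages slightly below 12.
- Standardised change: 9/12 = 0.75 becomes 6.0/10.7 = 0.56.

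**5. Over the assumed range.** The SE with zeros is about 0.7 to 0.9 times the observed-case SE. A nominal 95% interval around the diluted mean covers the true mean change in 29% to 88% of simulated samples, mainly because the centre has moved. The SD is not always reduced. The variance formula simplifies to 0.667 SD² + 0.230 μ², which is below SD² only when |μ| is less than about 1.2 SD. At μ = -15 and SD = 10 the SD rises to 10.9.

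**6. Choice of test.** The protocol names no normality test; Shapiro-Wilk at 5% is used here as an example. In the worked case it rejects in about 83% of samples with the zeros. Over means of 0 to -15 the figure is 66% to 98%, against about 4% to 6% without the zeros.

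**7. Effect on the test decision.** With SD 12:

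| Mean change | t-test, 30 values with zeros | Signed-rank, 20 non-zero values |
|---|---|---|
| 0 | 4.3% | 3.9% |
| -6 | 57% | 56% |
| -9 | 88% | 87% |
| -12 | 99% | 99% |

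The two tests reached the same decision in 94% to 99.6% of runs. The t-test also rejects about equally often with and without the zeros (mean -5, SD 12: 41.2% against 41.6%), because mean and SE shrink together.

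**8. The competing rule.** Under the withdrawal section, a participant lost to follow-up meets a discontinuation criterion and the data are removed. The 10 zeros do not arise, the analysis holds about 20 people, and LOCF has almost nothing left to fill. The protocol does not say which rule takes precedence.

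**The case against.** A reader might infer that the plan will certainly give a third of participants a zero change. The documents do not support that, for three reasons. First, the withdrawal section would take these participants out, and the sample-size section speaks of obtaining data from 20, which suggests that dropouts were not expected to supply data. Second, the primary outcome is a change, so a measurement of it can be read as requiring a post-baseline value. Third, 67% is the clinic's general return rate; participants are paid for visits 1 to 3 and contacted individually, so retention may be better.

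A reader might also infer that the p-value is corrupted or a blood-pressure effect manufactured. Neither holds: test decisions barely change, and zeros pull an observed reduction toward no effect. The protocol does not promise a confidence interval, and it states that determining efficacy is not its purpose. An analysis plan, not shown here, could settle the FAS wording.

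These points limit the claim without removing it. The follow-up condition in the Safety Set makes its absence from the FAS count for the literal reading. The withdrawal rule does not cure the LOCF rule; it contradicts it, and it also sits badly with an FAS said to follow intention to treat. For a preliminary study, a diluted estimate with too small an SE is a real fault even when the test against zero survives.

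**Conclusion.** The concern holds in conditional form. Applied as written, the FAS and LOCF rules allow a baseline-only participant to be scored as exactly unchanged, possibly about 10 of 30 at the protocol's planning rate and fewer with better retention. The withdrawal section would remove the same people, so the size of the primary analysis set is undetermined between about 20 and about 30.

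If LOCF governs, the mean change is cut by one third and its SE understated: from -9 to -6.0 mmHg, with a half-width of 4.0 instead of about 5.5 mmHg, under the assumed mean and SD. The normality-driven choice is pushed toward a test that usually omits the zeros. The damage lies in the estimate, the SD and any interval carried into later planning. This should be fixed, but in an uncontrolled exploratory study it does not invalidate the design.

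**What to change.** 1. Reconcile the FAS definition, the LOCF sentence and the withdrawal section. State that data collected before loss to follow-up are kept where consent allows, and separate loss to follow-up from withdrawal of consent to data use.
2. Do not carry baseline forward in the primary analysis. Either estimate the visit 3 minus visit 1 change from observed data with a repeated-measures mixed model on visits 1 to 3, stating that it relies on missing at random, or define the FAS as requiring a post-baseline MSSBP.
3. Report LOCF and completers as sensitivity analyses only, with the number of baseline-only participants shown.
4. Name one primary test in advance and drop the normality-driven switch for the primary outcome.

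The cost is a change of wording and a few lines of SAS code, with no extra visits or participants. The interval will be wider. The mixed model brings a missing-at-random assumption that cannot be verified from the data. The post-baseline FAS gives an estimate for all enrolled only if those who do not return resemble those who do.
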